No multiplicity adjustment will be applied to correct for the multiple treatment arms since the two active training conditions are distinct treatments, compared to their own control condition. As mentioned earlier, in order to efficiently explore the main effects of both types of training modules, the design of the study involves running two clinical trials under the same protocol. Hence, the two trials can be considered as separate studies, making it unconventional to apply any adjustments to alpha levels. Furthermore, we emphasize that the study is strictly explorative in nature, so any significant findings should be received with some reservation until tested in further confirmatory RCTs, implying a lesser need for multiple-testing correction [67].

If significant effects of the CBM interventions on the cognitive bias and gambling outcomes are detected, a moderated mediation analysis for each CBM module will be carried out to explore the moderating effect of interference control capacity, impulsivity and baseline cognitive bias on the relation between CBM effects and the gambling outcome(s) [68]. Baseline cognitive biases, interference control capacity (Stroop task) and trait impulsivity (BIS-11) would be tested as moderators of the changes in cognitive bias resulting from training, which would further act as mediator of the change in the primary outcome(s).

Besides monitoring participant inclusion and drop-out, the analysis plan does not involve any interim analysis of collected data. The clinical trial will continue until the target sample size is reached unless participant attrition rate, defined as a drop-out at any moment after completing the baseline assessment, exceeds the expected 60% attrition rate of included participants [42]. The results of the study will be reported following the guidelines of the “Consolidated standards of reporting trials” (CONSORT) extension to non-pharmacological interventions [69].

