### Sample size

A conservative a priori power analysis (G*Power 3.1, open-source software [70]) required a sample size of 114 participants to detect a small-to-medium effect size (Cohen’s *f* = 0.15, equivalent to partial eta squared value of 0.02) for the interaction effect between time and experimental condition for each primary outcome, using mixed ANOVA. Power of 0.80, Bonferroni-adjusted type-I error probability of 0.025 (0.05/2 primary outcomes) and moderate correlation between the repeated measures of 0.3 were assumed. Based on a similar online CBM study for alcohol drinking problems [42], an additional 60% dropout rate at follow up was taken into account, leading to a final target sample size of 182 participants.

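### The attrition stopping limit is set at the dropout rate the plan itself expects, so attrition exactly as planned puts the trial on its stopping boundary

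*Protocol article*

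**What the plan says.** Two sections of the protocol article use the same figure for different purposes.

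- **Stopping rule (Data analysis).** "The clinical trial will continue until the target sample size is reached unless participant attrition rate", which is "defined as a drop-out at any moment after completing the baseline assessment", "exceeds the expected 60% attrition rate of included participants". The limit is thus 60%, the text itself calls it the expected rate, and the stated denominator is the participants included.
- **Planning rate (Sample size).** The power analysis "required a sample size of 114 participants to detect a small-to-medium effect size". Then "an additional 60% dropout rate at follow up was taken into account", "leading to a final target sample size of 182 participants". The 60% is taken from the same cited online study as the stopping limit.

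Three other statements bear on how the rule would work. Study design gives about 7.5 months of participation per person. Data management describes regular inspection of activity logs, mainly for technical problems, inclusion and adherence, and yearly investigator meetings with a special focus on recruitment and drop-out. Trial status gives data collection from February 2015 to an expected end in late 2017.

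**The concern.** A rule that halts recruitment for excess attrition should separate attrition worse than planned from attrition as planned. A limit equal to the planning value cannot do so: when the assumption is exactly right, ordinary sampling variation decides whether the limit is crossed, and each further look adds another chance of crossing it.

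The denominator is a second difficulty. The planning rate describes people at the end of follow-up. A rate over everyone included so far also counts people who have had little time to drop out. It therefore understates final attrition by an amount that depends on accrual and on when people leave.

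At stake is recruitment ended without cause on one reading, and a rule that is slow to see truly high attrition on another.

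**Working it through.** **1. The plan's own figures.** Interaction test, 2 groups by 4 time points, correlation 0.3, alpha 0.025, power 0.80. With partial eta squared 0.02, f² = 0.02/0.98 = 0.0204. The noncentrality at N = 114 is 0.0204 × 114 × 4/(1 − 0.3) = 13.3 on 3 and 336 degrees of freedom, and power is 0.807. The smallest N is 113, or 114 with equal groups, so 114 is reproduced. The target follows as 114 × 1.60 = 182.4, reported as 182.

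**2. What 182 delivers at 60% dropout.**
- Completers: 182 × 0.40 = 72.8, about 73.
- Enrolment needed to keep 114: 114/0.40 = 285.
- Dropout at which 182 still keeps 114: 1 − 114/182 = 37.4%.

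**3. Chance of exceeding 60% when the true rate is 60%, on participants with complete follow-up.** Dropouts are assumed independent. The smallest counts above 60% are 37 of 60, 73 of 121 and 110 of 182. The look sizes are illustrative thirds of the target.

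| Looks | Probability |
|---|---|
| 182 only: P(X ≥ 110), X ~ Bin(182, 0.6) | 0.48 |
| 60 and 121 | 0.61 |
| 60, 121 and 182 | 0.67 |

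The first row is not a chance of early stopping, since the target has then been reached. The third row partly shares that limitation. With true attrition of 55%, better than planned, looks at 60 and 121 still cross the limit with probability 0.24.

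**4. The same rule on everyone included so far.** Assume steady accrual. If the 60% who leave do so uniformly over 7.5 months, the expected crude rate at month T (T ≥ 7.5) is 0.60 × (1 − 3.75/T).
- Month 12: 0.60 × 0.6875 = 41%.
- Month 24: 0.60 × 0.844 = 51%.

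If they leave uniformly within the first month, it is 0.60 × (1 − 0.5/T), or 57.5% and 58.8%. The same true rate thus gives quite different readings against one limit.

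Simulated chance of crossing at yearly looks (months 12 and 24), with an assumed 35-month accrual and true attrition 60%:

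| When dropout occurs | Probability |
|---|---|
| Uniform over 7.5 months | about 0.02 |
| Decaying, time constant 1.5 months | about 0.25 |
| Within the first month | 0.48 to 0.55 across simulations |

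The dilution also hides a real problem. With true attrition of 80%, uniform over follow-up, the expected crude rate at month 12 is 0.80 × 0.6875 = 55%, still under the limit.

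**5. A limit with a margin.** Require the Wilson lower 95% limit to exceed 60%. The smallest qualifying counts are 44 of 60 (73%), 84 of 121 (69%) and 123 of 182 (68%). With true attrition of 60%, the chance of crossing at any of the three looks is about 0.05.

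**The case against.** **What stands against the point.** The study is a pilot and calls itself explorative, and a feasibility limit at the expected rate can be a deliberate choice. The article is condensed, so a look schedule or minimum number may be in the full protocol; their absence here is not held against the plan. Continuous monitoring should not be assumed either. Applying the rule after every participant from n = 30 gives about 0.85, but the article ties attention to drop-out rates to yearly meetings and does not say that the rule is applied at each log inspection.

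**Stronger readings a reader might infer.**
- *Early stopping is more likely than not.* This is not established. The single full look gives 0.48 and stops no recruitment. Values above one half need repeated looks at completed follow-up or very early dropout. On the literal denominator the chance can be close to zero.
- *The sample size already allows for 60% dropout, and the rule takes that sample away.* It does not: 182 is 114 × 1.6. On a completer basis the required 114 is lost once dropout passes about 37%, well before the rule acts.
- *The rule uses a stricter dropout definition than the sizing.* This is weak. If dropout is permanent, leaving at any moment after baseline, assessed through the last visit, is the same event as dropout at follow-up, and both passages rely on the same source.

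None of this removes the core point. The article fixes both the limit and the planning value at 60%, and pilot status does not explain a rule that chance alone can trigger when the plan's assumption is met.

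**Conclusion.** The point holds in this form: the stopping limit equals the expected rate, with no margin, and its stated denominator does not match the rate it is compared with. With true attrition of 60%, the limit is crossed with probability 0.61 at looks of 60 and 121 participants with complete follow-up. On everyone included so far, at yearly looks, the probability is about 0.02 to 0.55.

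The identity of the two 60% figures and the single-look 0.48 need nothing beyond the article and independent dropouts. The look sizes, the 35-month accrual and the dropout timings are assumptions, and the width of the range reflects them. The documents do not support a claim that the trial will probably stop early. They support saying that the rule can end recruitment when nothing unexpected has happened, and that how often it does so depends on details the stated sentence does not settle.

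**What to change.** Amend the stopping sentence in Data analysis so that:

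1. attrition is judged at the yearly reviews already scheduled;
2. the rate is taken among participants whose 6-month visit is due;
3. stopping is considered only when attrition is clearly above the expected rate, for example when the lower 95% limit exceeds 60%.

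Set the limit together with a corrected statement in Sample size of what 182 delivers: about 73 completers at 60% dropout, and 114 only up to about 37% dropout. The example limit would tolerate up to 122 dropouts among 182, leaving 60 completers, so the investigators should decide how many completers are still worth having and choose the limit accordingly.

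The change costs one amended sentence and the sample-size correction. The price is later action on truly higher attrition. At a true rate of 70%, the present limit is crossed by the look at 121 with probability 0.99, while the example limit (44 of 60, or 84 of 121) is crossed with probability 0.63. Both figures are exact binomial calculations on complete follow-up. Waiting for 6-month visits adds a further delay of about the length of participation.

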### Sample size

A conservative a priori power analysis (G*Power 3.1, open-source software [70]) required a sample size of 114 participants to detect a small-to-medium effect size (Cohen’s *f* = 0.15, equivalent to partial eta squared value of 0.02) for the interaction effect between time and experimental condition for each primary outcome, using mixed ANOVA. Power of 0.80, Bonferroni-adjusted type-I error probability of 0.025 (0.05/2 primary outcomes) and moderate correlation between the repeated measures of 0.3 were assumed. Based on a similar online CBM study for alcohol drinking problems [42], an additional 60% dropout rate at follow up was taken into account, leading to a final target sample size of 182 participants.

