The maladaptive selective information processing and conditioned mechanisms underlying problematic and pathological gambling suggest that CBM paradigms may also be effective in reversing gambling-related cognitive biases, thus potentially reducing affective reactivity and changing habitual behaviours [13, 16, 24, 37]. To date there is no study exploring the effectiveness of CBM for GD. However, a first pilot study in another form of behavioural addiction, online gaming, reported that a single session of AppBM decreased gaming-related approach bias and positively affected gaming behaviour [38].

CBM interventions can in principle be administered online, thus showing potential of being a low-threshold, low-cost addition to more conventional treatments, such as cognitive behavioural therapy and motivational interviewing. This CBM feature is of particular value for new gambling treatment venues, since only 10% of problematic and pathological gamblers seem to seek help and enter treatment [39], likely because of shame and stigma about their condition or because they are unaware, reluctant, or unavailable to start face-to-face treatment [40, 41]. Providing web-based interventions can then increase the accessibility to help-resources for gamblers by ensuring anonymity and circumventing many of the barriers associated with traditional in-person treatments. However, there are indications that online CBM interventions may be less effective than clinical interventions [42], although a recent trial in smoking cessation provided promising results [43].

The present paper reports the full design of a pilot randomised controlled trial (RCT) exploring the potential effectiveness of ABM training and AppBM training delivered online. For efficiency reasons, the two training modules are tested under the same protocol, each one compared to its own control condition, which is analogous to running two studies simultaneously. In addition to the training programme, all participants receive personalised motivational feedback on their motives to gamble and reasons to reduce or quit gambling, in order to support their compliance wth the training intervention [44] and promote the intrinsic motivation to change their gambling behaviour [45].

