#### Randomisation

Upon completing the baseline assessment session, participants are automatically randomised by the computerised system into one of the four experimental conditions in two steps: first, participants are randomised into three main experimental arms (ABM, AppBM, or placebo) with a 1:1:1.25 allocation ratio. Participants assigned to the placebo condition are then further randomised to receive the placebo version of either the AppBM or the ABM training, with a final allocation ratio equal to 1:1:0.62:0.62. Both randomisation steps are stratified by gender (i.e., participants are randomly allocated to one of the conditions to which the fewest participants of their gender have been assigned so far). The two-step randomisation procedure and the uneven ratio over the four experimental conditions were designed to increase the chance of receiving at least one active training intervention, while still allowing for a univocal comparison of each active training module with their respective placebo condition. Allocation concealment is fully ensured, since participant randomisation is fully automated and performed by a computer algorithm.

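### The 114 is the total for one active-versus-placebo comparison, but the 182 recruits are shared by two, so neither comparison has the stated power of 0.80

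*Protocol article*

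**What the plan says.** The Sample size section states that the calculation "required a sample size of 114 participants to detect a small-to-medium effect size", namely Cohen's f = 0.15, described as "equivalent to partial eta squared value of 0.02". The effect to be detected is specified "for the interaction effect between time and experimental condition for each primary outcome, using mixed ANOVA". Power is 0.80, alpha is 0.025 (0.05 shared between two primary outcomes), and a "moderate correlation between the repeated measures of 0.3 were assumed". A 60% dropout allowance then takes 114 to 182, which the Abstract gives as the size of the whole trial.

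The Data analysis section specifies the primary model as a 2 (condition) × 4 (time) mixed ANOVA run separately for each training module, with each active arm set against its own control. The Background describes the modules as "each one compared to its own control condition, which is analogous to running two studies simultaneously". The Data analysis section repeats the argument when it declines a multiplicity adjustment: "Hence, the two trials can be considered as separate studies". Under Randomisation, the sample is divided over four arms "with a final allocation ratio equal to 1:1:0.62:0.62".

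**The concern.** A sample size has to match the comparison it is meant to power. If 114 is the requirement for one training against its placebo, a trial with two such comparisons and no shared control needs 114 evaluable participants twice. The article inflates 114 once and then divides the result between the two comparisons. It therefore treats the modules as two studies when it sets alpha and as one study when it sets the sample size.

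The stated power of 0.80 is the only guide a reader has to what a null result means. The Data analysis section asks for reservation about significant findings but gives no warning about non-significant ones. The article presents this as the first trial of these trainings in gambling, so a null result from a comparison with far less power than stated could be taken as evidence that a training does not work. The moderated mediation analysis is also conditional on significant effects, so low power would often stop it from being run.

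**Working it through.** **Inputs.** From Sample size: alpha = 0.025, power = 0.80, rho = 0.3, f = 0.15 or partial eta squared = 0.02, dropout = 60%, N = 114 inflated to 182. From Data analysis: k = 2 groups and m = 4 time points per module. From Randomisation: 1:1:0.62:0.62, where 0.62 is 1.25/2 = 0.625 rounded.

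**Formula.** The G*Power test for a within-between interaction, with sphericity assumed:

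- λ = f² × N × m / (1 − rho)
- df1 = (k − 1)(m − 1)
- df2 = (N − k)(m − 1)
- power = P(noncentral F(df1, df2, λ) > F at 1 − alpha)

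**Step 1: what the 114 is.** Partial eta squared 0.02 gives f = √(0.02/0.98) = 0.1429. With k = 2, m = 4 and N = 114, λ = 0.02041 × 114 × 4 / 0.7 = 13.29 on 3 and 336 degrees of freedom, and power is 0.807. N = 112 gives 0.799. The smallest N is 113, or 114 with equal groups, so the article's figure is reproduced.

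Smallest total N with four time points:

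| Groups | f = 0.1429 | f = 0.15 |
|---|---|---|
| 2 | 113 (114 with equal groups) | 102 |
| 3 | 140 | 127 |
| 4 | 160 | 146 |

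Fewer time points do not give 114 either: two groups over three times need 122 to 134, and over two times 152 to 166. At alpha 0.025 and rho 0.3, among two to four groups and two to four time points, only the two-group, four-time model with partial eta squared 0.02 gives 114. That is the model the Data analysis section specifies for one module.

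**Step 2: how many each comparison gets.**

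- 182 / (1 + 1 + 0.625 + 0.625) = 182 / 3.25 = 56 per active arm
- 56 × 0.625 = 35 per placebo arm
- 56 + 35 = 91 randomised per comparison
- At 60% dropout, equal in both arms: 91 × 0.4 = 36.4, or about 22 active and 14 placebo

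**Step 3: power per comparison** (k = 2, m = 4, alpha 0.025, rho 0.3). The ranges run from f = 0.1429 to f = 0.15. The last column scales λ by 4 × (56/91) × (35/91) = 0.947 for the unequal split.

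| Participants with complete data | Balanced | At 56:35 |
|---|---|---|
| 91 (no dropout) | 0.69 to 0.74 | 0.66 to 0.71 |
| 36.4 (60% dropout) | 0.26 to 0.29 | 0.25 to 0.28 |

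With 36 completers, the effect detectable with power 0.80 is f of about 0.26, against the stated 0.15.

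**Step 4: separating the two faults.** The step from 114 to 182 is 114 × 1.6 = 182.4. Keeping 114 after 60% dropout takes 114/0.4 = 285. Had the trial recruited 285, 114 would complete, 57 per comparison, and power would be 0.44 to 0.49. That is the effect of the two-comparison fault alone. The further fall to 0.25 to 0.29 comes from the dropout arithmetic.

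**Step 5: what 0.80 would take.** 114/0.4 = 285 randomised per module, or 2 × 285 = 570 in all.

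**The case against.** **The low figure mixes two faults.** This is right. The 0.25 to 0.29 needs both the shared 114 and the 114 × 1.6 inflation. The shared 114 is still enough on its own to break the claim: power is 0.44 to 0.49 with dropout correctly inflated, and at most 0.74 if nobody drops out. Correcting only the dropout step would leave this error in place.

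**Completers are not the planned analysis set.** The Data analysis section plans multiple imputation for an intention-to-treat analysis, and attrition there means leaving at any time after baseline, so some dropouts will contribute later data. Thirty-six is therefore the pessimistic end. But imputation cannot supply more information than complete data on all 91, and that ceiling is still below 0.80. The article itself sizes the trial with a dropout allowance.

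**The power figures depend on rho and on how f is defined.** Both points are fair. At rho = 0.5 and f = 0.15, power would be about 0.42 with 36 and 0.89 with 91. The claim of 0.80 is made at rho = 0.3, however, and should hold there. The loss from unequal arms applies only if f is defined for equal groups; without it, the balanced column stands.

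**The trial is a pilot and exploratory.** A pilot need not have power of 0.80. But this article makes a formal claim of 0.80 for each primary outcome and calls the calculation conservative, and a stated power should be true. The label makes a lower figure easy to accept; it does not make the stated one right.

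**Conclusion.** The concern holds. The 114 is the total for one two-group, four-time comparison, and the trial's 182 are divided between two comparisons that are not pooled. Each has about 91 randomised participants, fewer than 114 even with full retention. Power per comparison is at most 0.74 with no dropout and about 0.25 to 0.29 among completers at the planned 60% dropout. With imputation the effective value lies between these limits, and all of that range is below 0.80.

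The figures rest on the article's alpha, correlation and effect size, on sphericity, and on equal dropout in the two arms of a comparison. The conclusion that each comparison has fewer participants than its stated requirement needs only the allocation ratio and the 114.

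**What to change.** In the Sample size section:

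- State that 114 evaluable participants are needed for each training module, not for the trial as a whole.
- Give the expected numbers per comparison: about 56 active and 35 placebo randomised, and about 22 and 14 completing at 60% dropout.
- Restate the power of each comparison as about 0.25 to 0.29 among completers, with an upper limit of 0.66 to 0.74 if nobody drops out, or give the detectable effect of f about 0.26 at 36 completers.
- Correct the dropout step at the same time, since 114 × 1.6 does not leave 114 after 60% loss.
- State one effect size: 114 follows from partial eta squared 0.02, whereas f = 0.15 gives 102.

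In the Data analysis section and the later report, add that a non-significant result for a module is not evidence of no effect, alongside the existing caution about significant findings.

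This costs only wording and a less favourable power statement, which fits the pilot and exploratory purpose. Design, recruitment and analysis need not change. Keeping the claim of 0.80 would instead require about 570 randomised participants under the article's own assumptions.

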#### Outcome measures

Primary outcome measures are changes in the past-month gambling frequency and expenditure (i.e., money spent on gambling, irrespective of winnings) as assessed at baseline, post-intervention, and both follow-up sessions. The secondary outcome measures include changes in attentional (VPT) and approach (AAT) bias scores from baseline to the 3-month follow-up. Changes in depressive symptoms (BDI-II) and severity of gambling problems (SOGS) from baseline to the follow-up sessions are also explored, although not included as main outcomes. Intervention credibility and expectancies are also assessed with the Credibility/Expectancy Questionnaire [66] during the second session of training, to evaluate participants’ general experience with the study.

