### Data analysis

Multiple imputation of missing data will be performed for intention-to-treat analyses. Before running all analyses, all variable distributions will be screened for normality assumptions and univariate outliers. The use of parametric or non-parametric statistical tests will be adjusted accordingly. Each training group will be compared to its control group to check for any baseline difference in demographics (e.g., age and gender), severity of gambling problems (SOGS), and alcohol use. When significant differences are found and the relevant baseline variables also correlate with the outcomes of interest, they will be added as covariates in subsequent analyses.

Changes in gambling frequency and expenditure from baseline to the 6-month follow up will be examined through two separate 2 (condition: active training vs. placebo) × 4 (time: baseline, post-intervention, 3-month and 6-month follow up) mixed analysis of variance (ANOVA) analyses, one per training module. Each CBM condition is contrasted against its control condition, with the baseline assessment as reference time point for the following time points.

Changes in gambling cognitive biases as a result of each CBM intervention will be explored with a 3 (time: baseline, post-intervention, 3-month follow up) × 2 (condition: active vs. placebo training) × 2 (stimulus category: gambling vs. control) mixed ANOVA for approach bias (i.e., AAT task) and a 3 (time: baseline, post-intervention, 3-month follow up) × 2 (condition: active vs. placebo training) × 2 (trial type: on top vs. after) mixed ANOVA for attentional bias (i.e., VPT task). Any change in depression symptoms and gambling problems would be explored using two 2 (condition: active vs. placebo training) × 4 (time: baseline, post-intervention, 3-month and 6-month follow-up) mixed ANOVA analyses, one per training module.

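### The two primary outcomes are planned at a Bonferroni 0.025 each; naming Holm's step-down for the analysis would keep 5% within each training module and add some power when both effects are real (optional gain)

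*Protocol article*

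**What the plan says.** The Outcome measures section names two primary outcomes: "Primary outcome measures are changes in the past-month gambling frequency and expenditure". The Sample size section powers the study "for the interaction effect between time and experimental condition for each primary outcome, using mixed ANOVA", with power 0.80, a "Bonferroni-adjusted type-I error probability of 0.025 (0.05/2 primary outcomes", and a repeated-measures correlation of 0.3. It arrives at 114 participants before dropout.

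The Data analysis section tests each outcome with a 2 (condition) × "4 (time: baseline, post-intervention, 3-month and 6-month follow up) mixed analysis of variance (ANOVA) analyses, one per training module". It gives no significance level and no decision rule for the pair of primary outcomes. On multiplicity it says "No multiplicity adjustment will be applied to correct for the multiple treatment arms", because the two modules are treated as separate studies. It adds that "the study is strictly explorative in nature" and that there is therefore less need to correct.

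So 0.025 is the only level the article attaches to the two primary outcomes, and it stands among the inputs to the power calculation.

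**The concern.** If the planning level is carried into the analysis, each outcome is judged against 0.025 whatever the other one shows. Suppose that in one module frequency gives p = 0.01 and expenditure p = 0.04. Under single-step Bonferroni only frequency is supported. Under Holm both are, with the same 5% protection.

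Frequency and expenditure describe the same behaviour, so a training that works could plausibly change both, and that is the situation in which Holm helps. The planned moderated mediation analysis starts from significant effects on bias and on the gambling outcome(s), so the rule could decide whether the second outcome is carried into it.

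**Working it through.** **Inputs.** From Sample size: alpha 0.025, power 0.80, Cohen's f = 0.15, described as "equivalent to partial eta squared value of 0.02", and repeated-measures correlation ρ = 0.3. From Data analysis: k = 2 groups and m = 4 time points per module. Not in the article: the correlation between frequency and expenditure, here assumed to range from 0 to 0.7. Sphericity and equal groups are also assumed.

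**Reproducing 114.** For the within-between interaction, λ = f²·N·m/(1 − ρ), df1 = (k − 1)(m − 1) = 3, df2 = (N − k)(m − 1).
- Partial eta squared 0.02 gives f = √(0.02/0.98) = 0.1429. The smallest N is 113, or 114 with equal groups, which matches the article. At N = 114, df2 = 336 and power is 0.807 at alpha 0.025 and 0.875 at alpha 0.05.
- With f = 0.15 the smallest N is 102 (power 0.800), and power at N = 114 is 0.851.

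**Error control.** Holm tests the smaller p-value at 0.025 and, only if that rejects, the larger at 0.05.
- Both nulls true: a false rejection needs the smaller p-value at or below 0.025, so its probability is at most 2 × 0.025 = 0.05. It is 1 − 0.975² = 0.0494 if the tests are independent, exactly as for Bonferroni.
- One null true: a false rejection needs that p-value at or below 0.05.
- Neither bound uses the correlation between outcomes. In simulation (20,000 runs, N = 114, f = 0.15) the Holm family-wise error was 0.043 to 0.048 with both nulls true and 0.045 to 0.048 with one.

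Any p-value at or below 0.025 is rejected by both procedures, so Holm loses no rejection.

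**Power, independent outcomes, N = 114, f = 0.1429.** Write p₁ = 0.8074 (at 0.025) and p₂ = 0.8746 (at 0.05).
- Per outcome: Bonferroni p₁ = 0.807; Holm p₁ + (p₂ − p₁)·p₁ = 0.8074 + 0.0672 × 0.8074 = 0.862.
- Both: Bonferroni p₁² = 0.652; Holm p₂² − (p₂ − p₁)² = 0.7649 − 0.0045 = 0.760.
- At least one: 1 − (1 − p₁)² = 0.963 under either.

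At exactly 0.80 power (N = 102, f = 0.15) the same formulas give 0.800 to 0.855 per outcome and 0.640 to 0.751 for both.

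**Power, correlated outcomes, simulated, N = 114, f = 0.15** (per outcome is the mean of the two):

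| Correlation | Per outcome, Bonferroni → Holm | Both, Bonferroni → Holm | At least one, either rule |
|---|---|---|---|
| 0 | 0.855 → 0.902 | 0.734 → 0.828 | 0.977 |
| 0.3 | 0.851 → 0.893 | 0.744 → 0.828 | 0.958 |
| 0.5 | 0.852 → 0.891 | 0.757 → 0.835 | 0.947 |
| 0.7 | 0.852 → 0.888 | 0.779 → 0.850 | 0.926 |

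Across these cases the gain per outcome is about 3.5 to 5.5 points (4 to 6 when rounded), and for both outcomes about 7 to 11 points.

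**Only one effect real.** Holm helps the real effect only when the null outcome is rejected first. With independent outcomes and f = 0.15 the gain is 0.025 × (0.9068 − 0.8512) = 0.0014; the simulation gave 0.850 against 0.851.

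**Sample size.** Holm's first step is also at 0.025, so planning at that level still gives 114.

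**The case against.** The strongest reply is that the article does not say the outcomes will be analysed at a fixed 0.025. That stands. The figure is a power-calculation assumption, Data analysis names no level, and planning at 0.025 is compatible with a Holm analysis. A reader might infer a stated decision rule, but it is only implied. The step-wise procedure may also sit in a full protocol or analysis plan that is not shown, so its absence from the article is not a fault.

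Second, Bonferroni at 0.05/2 is valid and arithmetically exact. Nothing in the Sample size section is wrong on this point. The exploratory aim also lowers the stakes: nothing in the article requires significance on both outcomes.

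Third, three larger claims are tempting and fail.
- That Holm makes a positive finding more likely: the chance of at least one significant outcome is identical.
- That Bonferroni wastes most when the outcomes are strongly correlated: the gain for both outcomes falls from 9.4 points at correlation 0 to 7.1 at 0.7. What matters is that both effects are real.
- That the change is free: Bonferroni has simple matching simultaneous confidence intervals and Holm does not.

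What survives is narrower. The only level given for these outcomes points to single-step Bonferroni, and an equally protective procedure rejects at least as often. The article's own view that less correction is needed fits poorly with the more conservative of two valid rules.

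**Conclusion.** The point holds as an optional efficiency gain. With both effects real and power near the planned 0.80 to 0.85, Holm adds about 4 to 6 points of power per outcome and 7 to 11 points for supporting both. The sizes assume a correlation between outcomes of 0 to 0.7, sphericity, equal groups and the article's effect size; the error control does not depend on these.

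The gain depends on the power actually reached. The 114 is the requirement for one two-group comparison, whereas the 182 are spread over both modules, 91 each. With about 36 per module after 60% dropout and f = 0.15, power at 0.025 is about 0.29. For independent outcomes Holm then adds about 3 points per outcome (0.295 to 0.326) and 6 for both (0.087 to 0.150). That shortfall weighs far more than the choice between Holm and Bonferroni, and is a separate matter.

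A reader might also take 5% to cover the whole trial. It does not: with no adjustment across modules, four tests at 0.025 allow up to 0.10 (1 − 0.975⁴ = 0.096 if independent), and Holm within each module leaves that as it is.

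**What to change.** Add one sentence to Data analysis: within each training module, the time × condition tests for frequency and expenditure are judged by Holm's step-down at family-wise 0.05. In Sample size, keep 0.025 and describe it as the conservative first-step level used for planning. The same sentence would settle which level applies to the two primary outcomes.

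The change should be made before outcome data are examined. It needs no new data and does not alter the 114. Holm works on p-values, so it still applies if the planned distribution checks lead to non-parametric tests. The cost is that any simultaneous intervals shown beside the tests would no longer match the decision rule as simply as under Bonferroni. This is minor here, because the primary test is a three-degree-of-freedom interaction with no single interval of its own.
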